### Participant timeline {13}

Pregnant women will participate in the study from the first antenatal echography until the end of the first 1000 days of their child’s life. The evaluation time points are enrolment in the study (T0), end of the second trimester (T1), end of the third trimester (T2), and the postpartum period (T3). Data on app use will be collected throughout the study period. Other variables collected (T0) include data describing the population and potential confounders (e.g. age, country of origin, marital status and composition, socioeconomic level, educational level) and risk/protective factors (e.g. smoking and alcohol habits before pregnancy, data on current pregnancy).

Data collection will be based on self-completed questionnaires in paper form (T0, T1, T2) and online (T3), as well as data collected using information and management systems, and data on app use.

The questionnaires are provided as a Supplementary Material to this study protocol. Additional data to confirm vaccination adherence and to monitor access to and outcomes of preventive health, health promotion, and care can be accessed through the regional health information systems.

### Sample size {14}

Given that 55% of pregnant women living in Trieste received the DPT vaccine during pregnancy in 2018, and assuming that this rate increases to 70%, a sample size of 163 women per group (total of 326 women) with an alpha of 0.05 and a beta of 0.2 is required. Considering the possibility of spontaneous abortion and the possibility of losing participants during the follow-up period, the investigators determined to recruit 180 women per group (360 women in total).

### Recruitment {15}

Women attending the Unit of Fetal Medicine and Prenatal Diagnosis, IRCCS "Burlo Garofolo", in Trieste for the first echography of their pregnancy (around 12° gestational week (gw)) will be screened according to the inclusion and exclusion criteria outlined previously. The women concerned will be offered participation in this study. Recruitment will be kept open until the required sample size is reached; recruitment is expected to last 3.5 months. Since all women living in the area of Trieste will be required to visit the IRCCS "Burlo Garofolo" public health institute in Trieste for the first pregnancy echography, this will allow the researchers to reach the required number of participants.

## Assignment of interventions: allocation

### Sequence generation {16a}

Randomization will be open and will consider enrolment days. Eligible participants will be randomly assigned in a 1:1 ratio to the intervention group (use of the mHealth app) or to the control group (standard care). Enrolled women will be randomly assigned to two groups (the experimental group (A) and the control group (B)) using PC-driven randomization of enrolment days. This will facilitate enrolment as the researcher can give more information and train the groups of women to download and initialize the app.

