### Who will take informed consent? {26a}

Participants will be asked by the researcher to provide informed consent for study participation and data collection and management in accordance with the European General Data Protection Regulation (GDPR) and Italian law D.Lgs. 101/2018.

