### Concealment mechanism {16b}

Casualty of randomization will be ensured by hiding the randomized sequence in opaque and appropriately numbered envelopes.

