### Implementation {16c}

The researcher creates the random order, and participants are then enrolled according to the randomized tag.

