## Assignment of interventions: blinding

### Who will be blinded {17a}

None, this is an open-label study.

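### Allocating whole enrolment days openly undermines the concealment that the protocol claims for its envelopes: once a day's arm is revealed, later women that day are invited and consented with their arm known

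*Protocol article*

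**What the plan says.** Under Sequence generation {16a}, the protocol article says "Randomization will be open and will consider enrolment days", and that women are assigned 1:1 "using PC-driven randomization of enrolment days". The unit that receives an arm is therefore the day. The reason given is practical: "This will facilitate enrolment as the researcher can give more information and train the groups of women to download and initialize the app".

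Under Concealment mechanism {16b}, concealment is to come from "hiding the randomized sequence in opaque and appropriately numbered envelopes". The article does not say when an envelope is opened relative to consent.

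Under Implementation {16c}: "The researcher creates the random order, and participants are then enrolled according to the randomized tag". Under Who will take informed consent? {26a}: "Participants will be asked by the researcher to provide informed consent for study participation". The same role name thus appears for the sequence, for consent and, in {16a}, for information and training.

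Under Who will be blinded {17a}, the answer is "None, this is an open-label study". Under Statistical methods {20a}, the arms are compared by chi-square or Fisher's exact test without adjustment. Section {20b} plans no additional analysis.

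**The concern.** Concealment exists so that the decision to invite a woman, and her decision to consent, cannot depend on the arm she will get. An envelope does this when it is opened for one woman after she has been enrolled. Here one envelope settles a whole day. After it is opened, every further woman who comes for her scan that day is approached by staff who know what they are offering.

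There is room for selection. Two inclusion criteria call for judgement or stated intention: a good understanding of Italian, and willingness to deliver at the Institute. The offer itself also differs, because on app days it can be presented with the app and on control days without it. Women who accept on the two kinds of day may therefore differ in their inclination to be vaccinated before anyone has used the app.

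This is selection at entry, and it is distinct from the acknowledged lack of blinding after entry. Analysis by randomised group does not repair it, because the groups would already differ when they are formed.

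**Working it through.** **1. The plan's own sample size.** Inputs from Sample size {14}: 55% versus 70%, alpha 0.05, beta 0.2. Taking alpha as two-sided (the article does not say), with pooled variance under the null and no continuity correction:

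n = [1.960·√(2·0.625·0.375) + 0.842·√(0.55·0.45 + 0.70·0.30)]² / 0.15² = 162.3, rounded up to 163 per group.

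This matches the stated 163, so the sample size arithmetic is not at fault. The 163 is used in step 4.

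**2. Women per recruiting day.** Inputs: 360 women (Sample size {14}) and 3.5 months (Recruitment {15}). Recruiting days per week are not given, so they are an assumption.

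Weeks = 3.5 × 365.25 / 12 / 7 = 15.2. Days = 15.2 × days per week. Women per day m = 360 / days.

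**3. Share enrolled after the day's arm is known.** Suppose the envelope is opened at the consent of the day's first woman. Only that woman is protected, so the share is 1 − 1/m.

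| Recruiting days per week (assumed) | Days | m | 1 − 1/m |
|---|---|---|---|
| 7 | 106.5 | 3.4 | 70% |
| 5 | 76.1 | 4.7 | 79% |
| 3 | 45.7 | 7.9 | 87% |

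Allowing daily numbers to vary as Poisson gives 71%, 79% and 87%, almost the same. Two other cases bound the result:
- If the enroller knows the list, or opens the envelope at the start of the day, the share is 100%.
- If all women of a session consent before the envelope is opened, the share for that session is 0%.

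The article does not say which case applies.

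**4. What an entry imbalance would do (hypothetical).** The documents give no size for such an imbalance. Take 163 per arm, no app effect, 55% uptake on control days and 55% + b on app days. With p̄ the mean of the two rates, SE₀ = √(2p̄(1−p̄)/163) and SE₁ the unpooled standard error:

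P(reject) = Φ[(b − 1.96·SE₀)/SE₁] + Φ[(−b − 1.96·SE₀)/SE₁]

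- b = 0: 0.025 + 0.025 = 5.0%.
- b = 0.03: SE₀ = SE₁ = 0.0549; 0.0786 + 0.0061 = 8.5%.
- b = 0.05: SE₀ = 0.0548, SE₁ = 0.0547; 0.147 + 0.002 = 14.9%.

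For scale, the targeted effect is 15 points. An imbalance in the other direction would inflate the error equally and would mask a benefit.

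**5. The sections side by side.** Section {16b} claims a hidden sequence. Section {16a} gives a day one arm, so that the researcher can act on it with groups of women. Section {16c} has women enrolled according to the tag, which reads as allocation before enrolment. Section {16a} also speaks of enrolled women being assigned, which reads as the reverse order. No sentence settles the order.

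**The case against.** The strongest reply is that the article does not show the envelope being opened too early. Assigning enrolled women and training them in groups is compatible with taking consent from a whole session and only then revealing the arm. The word open may mean no more than open-label. An article may also leave the time of opening and the keeper of the list to the full protocol, which is available on request. This limits what can be asserted: the 79% depends on when the envelope is opened. It does not remove the point, because {16a} and {16c} imply opposite orders and the concealment claim in {16b} depends on which one holds.

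A reader might infer that the person who makes the sequence also enrols the women. The documents do not establish this. Section {16c} puts enrolment in the passive, and the link to consent and training rests only on a shared role name.

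A reader might also infer that the envelopes conceal nothing. That goes too far. With a separate list keeper and opening at first consent, they still protect each day's first woman (about 21% of women at five days a week) and hide the arms of future days.

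Some safeguards deserve credit. Women attending the first scan are to be screened and those eligible offered participation, a datasheet covers all women invited ({18a}), and baseline characteristics are compared between arms. These steps narrow selection or make it visible; they do not remove it from an unadjusted test.

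It is tempting to add that T0 answers may be given with the arm known, since the app is installed at the same time. That does not reach the primary outcome, which is DPT vaccination assessed at T3.

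**Conclusion.** The concern holds in a limited form. Day-level open allocation is at odds with the concealment claimed, and no written rule puts consent before the reveal or separates the sequence maker from the enroller. At an assumed five recruiting days a week, about 79% of women would be enrolled with the arm known (70% to 87% at seven to three days). This rests on 360 women spread over 3.5 months and on opening at the day's first consent.

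The possible bias falls on the primary comparison and could not be undone after enrolment. The documents do not show that it will occur, or in which direction. The type I error of about 8.5% to 15% illustrates an assumed imbalance of 3 to 5 points and is not an estimate for this trial.

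**What to change.** 1. Have someone who is not involved in enrolment generate and hold the sequence, and say so in {16c}.
2. State in {16b} that the allocation is opened only after signed consent and a completed T0 questionnaire. This can be done with one numbered envelope per woman or, if day allocation is kept for group training, by opening the envelope after all women of that session have consented and completed T0. Women who arrive after that opening should not be enrolled in the same session.
3. If neither is adopted, withdraw the concealment claim in {16b}.
4. From the datasheet on all invited women in {18a}, report consent rates and characteristics by allocated day.

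The cost is protocol wording and a reordering of the enrolment visit, in a trial that the article describes as not yet recruiting. App set-up would be less easily batched. Individual allocation may also mix arms within a session, with some risk of contamination, so the choice between the two forms in item 2 is a genuine trade-off. Separating the roles and putting consent and T0 before the reveal are needed under either form.

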## Statistical methods

### Statistical methods for primary and secondary outcomes {20a}

Categorical variables will be presented as absolute numbers and percentages; continuous variables will be presented as mean and standard deviation or median and interquartile range, depending on data distribution assessed visually and using the Kolmogorov–Smirnov test.

The main population characteristics of the participating women in both groups (age, marital status, living area, country of origin, socioeconomic level, educational and occupational level, etc.) will be compared to assess the effectiveness of randomization. Differences between the two groups on categorical outcomes will be assessed using the chi-square test or Fisher’s exact test, as appropriate. Comparisons between continuous variables will be made with nonparametric Student *T* or Mann–Whitney tests, as appropriate for the data distribution. The main analysis will be an ‘intention-to-treat design’: all randomized women with an available main outcome will be assigned to the associated group regardless of intervention. A per-protocol analysis will also be performed. A statistically significant difference will be considered to exist if the *p*-value is < 0.05.

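### Enrolment days are randomised, but the sample size and the tests treat women as individually randomised, so 80% power and 5% error hold only if there is no within-day correlation

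*Protocol article*

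**What the plan says.** **Allocation.** Protocol article, Sequence generation {16a}, states that "Eligible participants will be randomly assigned in a 1:1 ratio" and then gives the mechanism: women are placed in the two groups "using PC-driven randomization of enrolment days". The reason given is practical: the researcher can inform and "train the groups of women to download and initialize the app". Concealment mechanism {16b} adds numbered opaque envelopes, and Implementation {16c} says that women are enrolled according to the randomised tag.

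**Sample size.** Sample size {14} starts from local coverage ("Given that 55% of pregnant women living in Trieste received the DPT vaccine during pregnancy in 2018"), assumes a rise to 70%, and concludes that "a sample size of 163 women per group (total of 326 women) with an alpha of 0.05 and a beta of 0.2 is required". The target is then raised to 180 per group to allow for spontaneous abortion and loss to follow-up.

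**Analysis.** Statistical methods {20a} says "Differences between the two groups on categorical outcomes will be assessed using the chi-square test" or Fisher's exact test, with t or Mann–Whitney tests for continuous variables and significance at p < 0.05. None of these tests takes account of enrolment day. Methods for additional analyses {20b} plans nothing further.

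**The concern.** The stated reason for randomising days, training women together, works only if everyone enrolled on a day is in the same arm. That makes each day a cluster. The sample size and the tests count women as if each had been randomised separately.

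Women enrolled on the same day may share a clinic list, staff and calendar time and, in the app arm, the training session. If this makes their vaccination outcomes even slightly alike, 326 women carry less information than 326 independent women. The unadjusted test then understates the standard error and rejects a true null hypothesis more than 5% of the time, while a test that respects the clustering has less than the stated power. The main conclusion, on DPT vaccination in pregnancy, rests on this comparison.

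This is not a detail left to an analysis plan. The article itself fixes the allocation unit, the required number and the tests, and they do not fit together.

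**Working it through.** **Step 1: reproduce 163.** Inputs from Sample size {14}: 55% versus 70%, alpha 0.05, beta 0.2. Sidedness is not stated; two-sided reproduces the figure. With the pooled rate p̄ = (0.55 + 0.70)/2 = 0.625:

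n = [1.960·√(2·0.625·0.375) + 0.8416·√(0.55·0.45 + 0.70·0.30)]² / 0.15²
= (1.3419 + 0.5693)² / 0.0225 = 162.3, rounded up to **163 per group**.

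Other versions do not match: unpooled variance gives 160, a continuity correction 176 and a one-sided test 128. Power at 163 per group is 80.2%. The matching formula has a design effect of 1, that is, independent women.

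**Step 2: is clustering covered elsewhere?** The increase from 163 to 180 is a loss allowance of 1 − 163/180 = 9.4%, and the article assigns it to spontaneous abortion and loss to follow-up. It cannot also pay for a design effect.

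**Step 3: cluster size (assumed).** The article gives a recruitment period of 3.5 months but no number of enrolment days. 3.5 months is 3.5 × 365.25/12/7 = 15.2 weeks. Enrolment on every weekday gives about 75 days, or 326/75 = 4.3 analysed women per day. Two days a week gives about 30 days, or 326/30 = 10.9 per day.

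**Step 4: effect over an assumed ICC range.** The formulas are:

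- design effect DE = 1 + (m − 1)·ICC, where m is women per day;
- power of a cluster-adjusted test = two-proportion power at 163/DE per arm;
- type I error of the unadjusted test = 2·[1 − Φ(1.96/√DE)].

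| Days (m) | ICC | DE | Power | Type I error, formula |
|---|---|---|---|---|
| any | 0 | 1.00 | 80.2% | 5.0% |
| 75 (4.3) | 0.005 | 1.02 | 79.5% | 5.2% |
| 75 (4.3) | 0.01 | 1.03 | 78.8% | 5.4% |
| 75 (4.3) | 0.02 | 1.07 | 77.6% | 5.8% |
| 75 (4.3) | 0.05 | 1.17 | 73.8% | 7.0% |
| 30 (10.9) | 0.01 | 1.10 | 76.3% | 6.2% |
| 30 (10.9) | 0.02 | 1.20 | 72.7% | 7.3% |
| 30 (10.9) | 0.05 | 1.49 | 63.0% | 10.9% |

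Example, 30 days and ICC 0.05: DE = 1 + 9.87 × 0.05 = 1.49, effective n = 163/1.493 = 109 per arm, power 63.0%. Holding 80% power there would need 163 × 1.493 = 243.4, so 244 per arm.

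**Step 5: check the error rate by simulation.** Beta-binomial simulation of the unadjusted test agrees with the formula when days are of equal size. Unequal day sizes push the error up a little: at about 75 days, 6.3% (ICC 0.02) and 7.8% (ICC 0.05); at 30 days, 7.4% and 11.4%.

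The power figures use equal day sizes and a normal approximation. Unequal days and a small-sample correction would lower them somewhat further.

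**The case against.** The strongest reply is that the within-day correlation may be close to zero. These are days in one clinic, not separate hospitals. Women enrol around week 12, and the outcome is each woman's own vaccination during pregnancy, assessed after birth. After help with installation she uses the app on her own phone, usual care is the same in both arms, and group training takes place in the app arm only. One shared visit is a weak source of similarity in a later vaccination decision. With weekday enrolment and an ICC of 0.005 to 0.01, power falls by about one point and the error rate rises by well under one point. The 30-day schedule is also an assumption that nothing in the article supports.

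All of this stands as a limit on size. A reader might infer that the 80% and 5% figures are definitely wrong, or that true power is near 63%. The documents support neither: both need a positive ICC, and the second also needs few enrolment days.

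What does not stand is that the mismatch is harmless by default. Zero correlation is the only value at which 163, 80% and 5% all hold, and the article does not claim it.

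A second reply is that the 1:1 sentence, the envelopes and the tag point to individual randomisation. They are equally compatible with tagged days, and none describes a separate draw for each woman. If individual randomisation was meant, the allocation text is wrong and still needs correcting.

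**Conclusion.** The concern holds in conditional form. The unit of allocation is the enrolment day, the unit in the sample size and the tests is the woman, and nothing in the article bridges the two. The stated power and error rate are valid only without within-day correlation.

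With 163 per arm analysed, the departure ranges from negligible (about 79% power and 5.5% error at 75 days and ICC 0.01) to material (about 63% and 11% at 30 days and ICC 0.05). Where the trial falls in that range depends on the ICC and the number of days, and the documents give neither. Confidence is high that the mismatch exists; its size is open.

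**What to change.** - **Sequence generation {16a}:** name the enrolment day as the randomised unit.
- **Statistical methods {20a}:** replace the unadjusted tests with a day-level analysis, or with a GEE or mixed model clustered on enrolment day, using a small-sample correction.
- **Sample size {14}:** restate power with the expected number of enrolment days, the women per day and an ICC range that includes 0 to 0.01. Decide from that whether the target needs to rise.

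If individual randomisation was intended, or is adopted now, correct Sequence generation {16a} instead; the sample size and tests then stand as written.

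The cost is slightly more analysis work and a somewhat less favourable stated power. Enrolment day has to be known for each woman in any case, because it determines her arm. Moving to individual randomisation would give up the convenience of training a whole day's women together. Trial status says recruitment had not begun when the article was written, so at that point every option was open; once women have been enrolled by day, only the analysis and the power statement can be changed.

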### Concealment mechanism {16b}

Casualty of randomization will be ensured by hiding the randomized sequence in opaque and appropriately numbered envelopes.

### Implementation {16c}

The researcher creates the random order, and participants are then enrolled according to the randomized tag.

## Assignment of interventions: blinding

### Who will be blinded {17a}

None, this is an open-label study.

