### Trial design {8}

Randomized, open-label, controlled trial to prospectively evaluate the superiority of care delivered with the support of the mHealth app over standard care.

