## Methods: participants, interventions, and outcomes

### Study setting {9}

The study population is pregnant women attending the Unit of Fetal Medicine and Prenatal Diagnosis for first-trimester echography during pregnancy. Enrolment and subsequent data collection will be performed at Unit of Fetal Medicine and Prenatal Diagnosis, Institute for Maternal and Child Health - IRCCS "Burlo Garofolo", Trieste, Italy; analyses will be performed by Clinical Epidemiology and Healthcare Services Research, Institute for Maternal and Child Health - IRCCS "Burlo Garofolo", Trieste, Italy.

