### Outcomes {12}

The primary study outcome is the differences between experimental and control groups regarding adherence to DPT vaccination in pregnant women (questionnaires; evaluation at T3—postpartum period). The choice of this outcome is due to the clear evidence of the need for maternal vaccination, especially against pertussis, which can be a life-threatening infection for the newborn. Moreover, available data on DPT vaccination coverage among pregnant women in Trieste for the past years show an unsatisfactory percentage of women vaccinated with DPT (only 55%).

Secondary study outcomes are the differences between experimental and control groups in:Knowledge and behaviours in terms of health prevention and promotion, especially regarding folic acid intake, weight gain during pregnancy, smoking and alcohol consumption, breastfeeding, adherence to the routine childhood immunization schedule (questionnaires; evaluation at T1—end of the second trimester, T2—end of the third trimester, T3)Level of health literacy (Italian version of the 16-item European Health Literacy Survey Questionnaire HLS-EU-Q16; evaluation at T1, T2, and T3)Evaluation of the social and health impact of the introduction of an mHealth app for a maternal and child hospital (questionnaire; evaluation at T3)

As with the experimental group, the final evaluation will include:The appreciation of such a tool to bridge the information gap between patients and health institutions (qualitative satisfaction questionnaire, freely modified from the Mobile Application Rating Scale (MARS); evaluation at T3)Analysis of data on app use collected by the app itself throughout the study period

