## Data collection and management

### Plans for assessment and collection of outcomes {18a}

Baseline data on all women invited to participate will be collected in a datasheet to control for unwanted bias in language, age, or other variables at enrolment. Data collection will be based on self-completed questionnaires in paper form (T0, T1, T2) and online (T3), together with data collected through information and management systems and data about app use. An English-translated version of the questionnaires is provided a Supplementary material to this study protocol. Additional data to confirm vaccination adherence and to monitor access to and outcomes of preventive health, health promotion, and care can be accessed through the regional health information systems.

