### Data management {19}

Data entry for the printed questionnaires will be possible through a digital interface similar to that used for data collection during follow-up via the online survey. Each participant is linked to a unique participant code; duplicates will be checked after data entry. Data will be then merged with other sources, the utilization data, and the health information system to obtain the final complete data set.

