### Methods in analysis to handle protocol non-adherence and any statistical methods to handle missing data {20c}

The main analysis will be performed as an ‘intention-to-treat’. All randomized women with an available main outcome will be analysed in the group to which they were randomized, regardless of whether they received the assigned intervention. Reasons for dropping out of the study will be detailed, and the potential impact of missing data on study outcomes will be explored through sensitivity analysis.

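### The protocol leaves everyone unblinded because the trial is open-label, but that reason does not cover the check of vaccination status or the analysis, which could cheaply be done on coded arms

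*Protocol article*

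**What the plan says.** Under Who will be blinded {17a} the protocol article states: "None, this is an open-label study". The next section, on unblinding, gives the same reason. No section masks an outcome assessor, a data handler or an analyst.

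Four other places bear on this:

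- **Primary outcome.** Outcomes {12} defines it as "adherence to DPT vaccination in pregnant women (questionnaires; evaluation at T3—postpartum period"). Plans for assessment and collection of outcomes {18a} adds: "Data collection will be based on self-completed questionnaires in paper form (T0, T1, T2) and online (T3").
- **Second source.** The same section says of the regional health information systems: "Additional data to confirm vaccination adherence and to monitor access to and outcomes of preventive health, health promotion, and care can be accessed". Participant timeline {13} repeats this. The wording is permissive.
- **Merge.** Data management {19} says: "Data will be then merged with other sources, the utilization data, and the health information system to obtain the final complete data set".
- **Analysis.** Study setting {9} says "analyses will be performed by Clinical Epidemiology and Healthcare Services Research", a different unit from the one that enrols the women, in the same institute. Section {20c} adds that "the potential impact of missing data on study outcomes will be explored through sensitivity analysis".

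**The concern.** Open label describes what the women and the staff in contact with them know. Group A women are helped to install the app (Intervention description {11a}), so they and the enrolling staff cannot be masked. Nothing in that arrangement requires the arm to be visible to the person who compares a questionnaire answer with a vaccination record, or to the analyst.

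As written, it will be visible to both. The decision whether to look a woman up, what to do when the two sources disagree, how to handle awkward records in the main analysis, and what form the missing-data sensitivity analyses take could all be settled by people who know which group each woman was in. Any leaning, even an unintended one, could favour an app that the institute itself is introducing.

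This is a decision the protocol states, not a detail left to an analysis plan. A later plan that masked the analyst would contradict section {17a}.

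**Working it through.** **1. Does the stated reason reach the people concerned?**

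| Person | Must know the arm? | Why |
|---|---|---|
| Participant | Yes | Has the app or does not |
| Enrolling and installing staff | Yes | They help with the download ({11a}) and allocate by enrolment day ({16a}) |
| Whoever checks DPT status against the regional record | No | Needs only the answer and the record |
| Analyst, main comparison | No | Needs two group labels, not their meaning |

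The reason in {17a} supports the first two rows only.

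**2. Would removing the arm column be enough?** No. App-use data exist only for group A, and {19} merges them into the final file, so any row with such data shows its arm. Allocation is also by enrolment day ({16a}), so an enrolment date reveals the arm to anyone who knows the schedule. Both have to be held back.

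**3. The plan's own figure.** Inputs from Sample size {14}: 55% against 70%, alpha 0.05, beta 0.2. Two-sided, pooled variance under the null, no continuity correction, mean rate 0.625:

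n = [1.960 × √(2 × 0.625 × 0.375) + 0.842 × √(0.55 × 0.45 + 0.70 × 0.30)]² / 0.15² = (1.342 + 0.569)² / 0.0225 ≈ 162.3, rounded up to 163.

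This matches the stated 163 per group. Masking changes nothing here.

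**4. What a few reclassified women would do.** The documents give no rate of disagreement between questionnaire and record, so every count below is an assumption.

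- Three women in one arm: 3/163 = 1.8 percentage points, or 1.8/15 = 12% of the planned difference.
- Example: with 90/163 (55.2%) vaccinated in the control arm, moving the app arm from 105 to 108 changes the difference from 15/163 = 9.2 to 18/163 = 11.0 points. The uncorrected chi-square p-value goes from 0.090 to 0.041.
- No true effect, 55% in both arms, and a share m of unvaccinated app-arm women counted as vaccinated. The spurious difference is d = 0.45m and the app-arm rate is p₂ = 0.55 + d. The chance of a significant result favouring the app is 1 − Φ[(1.96·SE₀ − d)/SE₁], with SE₀ = √(2p̄(1 − p̄)/163), p̄ the mean of 0.55 and p₂, and SE₁ = √([0.55 × 0.45 + p₂(1 − p₂)]/163).

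| Assumed share m | Spurious difference (points) | False positive favouring app (nominal 2.5%) | Two-sided false positive (nominal 5%) |
|---|---|---|---|
| 1% | 0.45 | 3.0% | 5.1% |
| 2% | 0.9 | 3.6% | 5.3% |
| 5% | 2.25 | 6.0% | 6.9% |
| 10% | 4.5 | 12.7% | 13.0% |

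Three women are about 4.1% of the expected unvaccinated in one arm (3 / (0.45 × 163) = 3/73.35). That gives about 5.2% in the column for false positives favouring the app. These calculations treat women as individually randomised and show scale only. They do not estimate the bias in this trial.

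**The case against.** **Masking misses the main open-label risk.** The T3 status is self-completed by women who know their arm, and masking those who handle the answers later does not change the answers. This stands and limits the importance of the point.

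**No adjudication is described.** The protocol names the questionnaire as the source and gives the regional record only a confirming role. It names no adjudicator or data manager, and a fixed rule on which source prevails would leave little to judge. This stands in part: the role is inferred from the confirming step. But the article states no such rule, and with permissive wording even the choice of whom to check is made with the arm visible.

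**Analysis sits in a separate unit.** True, and it helps. It does not mask that unit, given the merged file.

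**Sensitivity-analysis detail may sit in an analysis plan.** Agreed, and its absence is not criticised here. The point is that {17a} leaves whoever settles it unmasked.

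A reader might also infer three stronger claims that the documents do not support:

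- *That masking would stop test-shopping between t and Mann-Whitney.* Two-sided p-values are the same with arms labelled X and Y, so prespecification cures that and masking does not. It also concerns continuous outcomes, and the primary outcome is binary.
- *That the exclusion for severe foetal malformation is part of this problem.* It arises during the study in enrolled women ({11b}), and nothing shows that the people masked here would make it.
- *That the per-protocol set can be fixed under masking.* If it depends on app use it cannot, because those data exist in one arm only.

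**Conclusion.** The point holds in limited form. The protocol's reason for blinding nobody does not extend to the check of vaccination status, the data handling for the main analysis or the sensitivity analyses, and the merged file makes the arm visible for all three. This avoidable exposure is separate from the women's own reporting bias, which would remain.

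The bias cannot be quantified from the documents. The 1.8 points rest on an assumed three reclassified women, and the table in the working rests on assumed shares. It would be wrong to read them as evidence that the result will be biased, or that the primary outcome turns on adjudicating two sources. The conclusion assumes that someone will use the regional record to confirm DPT status, as {13} and {18a} allow. The improvement is cheap and of minor to moderate importance.

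**What to change.** **Section {17a}.** State that participants and enrolling staff are not blinded, and that the check of vaccination status and the main analysis are done on arms coded X and Y.

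**Section {19}.** Have someone already on the study team, outside the analysis unit, prepare the export. The article names no such person, so the protocol should designate the role. The export should:

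- carry the arm as X or Y;
- keep app-use and app-appreciation data in a separate file, with any field showing that the T3 form came back through the app, since {11a} offers it there too;
- replace enrolment dates with a coded day identifier, because allocation is by enrolment day.

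**Breaking the code.** Do this only after vaccination status, the intention-to-treat set, and the main, secondary and sensitivity analysis scripts are locked. The app-use analysis, and any per-protocol set that depends on app use, come afterwards.

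**Cost.** Wording in two sections, a two-file export, and a later start for the app-use and per-protocol analyses. Enrolment, sample size, participant burden and care are unaffected. The article's Trial status section says recruitment has not begun, so the change can precede any data.
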